## Abstract

**Background:**

The benefits of physical activity are well established in people with multiple sclerosis (MS); yet, most people with MS are insufficiently active. Although many apps and devices are available to promote physical activity, these are not connected to electronic health records (EHRs), making it difficult for health care providers to prescribe and monitor their patients’ physical activity. The ExerciseRx platform is an innovative cloud-based, Health Insurance Portability and Accountability Act–compliant software platform (app+provider dashboard) that was developed to bridge the gap between consumer activity tracking devices, such as personal smartphones, and the EHR. The ExerciseRx app tracks a patient’s physical activity using their existing personal smartphone and provides a personalized graded progression in step count goals to increase step count gradually and safely over time. The ExerciseRx app also translates the activity data into actionable metrics on a provider dashboard within the EHR that the provider can use to make activity recommendations and monitor patients’ progress; they can also support patients by providing semiautomated weekly feedback and encouragement in meeting physical activity goals.

**Objective:**

This paper describes the protocol for a randomized controlled trial designed to understand whether the ExerciseRx digital health platform improves physical activity, symptoms, and functioning in adults with MS relative to a waitlist, usual care control.

**Methods:**

Participants are ambulatory adults with MS (n=106) who engage in <150 minutes per week of moderate to vigorous intense physical activity. Enrolled participants are assigned to use the ExerciseRx app for 12 weeks, versus a waitlist, usual care control. Participants allocated to the intervention condition have access to the ExerciseRx app, and their providers have access to the participants’ activity data via a provider dashboard, connected to the EHR. Participants allocated to usual care receive the care they would normally obtain at the MS Center, including encouragement to participate in and increase physical activity as tolerated from their clinical provider and a handout that describes the current physical activity recommendations for adults with MS and links to local and web-based resources suitable for MS. The primary outcome is the change in average daily step count throughout the 12-week intervention. Secondary outcomes include symptoms (fatigue intensity, pain intensity, sleep, and depressive symptoms), patient-reported functional outcomes (physical functioning, fatigue interference, pain interference, falls, and social participation), and qualitative analysis of participant and provider interviews on usability and acceptability of the ExerciseRx platform.

**Results:**

The study was funded in October 2023. Participant enrollment began in March 2024 and will continue through December 2025. As of July 25, 2025, a total of 85 participants have been enrolled in the trial. Data analysis and dissemination preparations will begin in January 2026.

**Conclusions:**

Results of this trial will provide important new information on the efficacy of an innovative digital health intervention tool for physical activity promotion.

**Trial Registration:**

ClinicalTrials.gov NCT06270641; https://clinicaltrials.gov/study/NCT06270641

**International Registered Report Identifier (IRRID):**

DERR1-10.2196/72213

## Introduction

Physical activity promotion is one of the most effective rehabilitation strategies for reducing multiple sclerosis (MS) symptoms and restoring health and functioning. Physical activity improves mobility, balance, fatigue, and depressive symptoms in people with MS [1-4]. Emerging evidence indicates that exercise also improves cognition, including attention, learning, memory, and executive functioning [5]. In addition to its importance in MS symptom management and overall health, regular physical activity may have disease-modifying effects [3,6]. Premorbid physical activity can predict disability progression over 2 years in people with MS [7], and moderate to vigorous levels of physical activity are associated with more normalized gray matter, white matter, and hippocampal volumes in people with MS [8]. Furthermore, a recent randomized clinical trial found that 24 weeks of progressive aerobic exercise resulted in lower MS relapse rates compared to waitlist controls [9].

Although physical activity is a stated priority for people with MS [10,11], approximately 80% of adults with MS do not get sufficient physical activity [12,13]. They are less active than the general US population [14], which is also sedentary [15]. For example, in a 2018 meta-analysis pooling 1355 adults with MS from 10 studies, adults with MS took significantly fewer steps per day relative to a nationally representative sample of 3752 adults [16]. Physical activity also decreases over time as the disease progresses [17] and is low even in those with mild disease or disability [12,14]. Barriers to exercise in this population include the physical effects of MS (eg, mobility impairment, imbalance, and weakness), common MS symptoms (eg, fatigue, depression, and pain), and psychosocial factors (eg, low exercise self-efficacy) [3,18]. Although physical activity is safe for people with MS [19], fears about its safety, potential to exacerbate MS disease, or falls may also present barriers [18]. The lack of community exercise facilities, the costs of gym memberships or wearables, transportation, and time restrictions are also barriers [18].

The National MS Society convened a panel of clinical and scientific experts to develop consensus recommendations for promoting exercise and lifestyle physical activity for people with MS across disability levels. Their 2022 recommendations included that: (1) health care providers (hereafter referred to as “providers”) routinely assess and promote the benefits of and engagement in exercise and physical activity for every patient with MS; (2) providers encourage >150 minutes per week of exercise or >150 minutes per week of lifestyle physical activity; and (3) exercise and physical activity should be advanced gradually, based on the individual’s preferences, abilities, and safety [18]. The guidelines emphasize the essential role of providers in promoting physical activity and encourage providers to support patients with strategies that increase physical activity, such as self-monitoring, goal setting, and accountability [16,18].

Despite a 2012 expert consensus panel recommending that providers incorporate physical activity promotion into comprehensive MS care [20], most people with MS report that their providers rarely discuss physical activity [10,21]. Importantly, adults with MS who met physical activity guidelines reported having providers who promoted physical activity, including through education and specific activity prescriptions, pointing to the central role that providers have in physical activity promotion [21,22]. Adults with MS prefer obtaining activity promotion information directly from their MS providers through patient-provider interactions. They are less interested in passive methods, such as receiving print (eg, handouts and pamphlets) or electronic information (eg, email and web-based) from their providers, although they appreciate having such information to supplement recall after the health care visit [23]. People with MS want their providers to give them up-to-date information about the benefits of activity and clear recommendations tailored to their disease severity, symptoms, and current activity level [10,22]. They also seek behavioral strategies to help incorporate physical activity into their daily lives, including goal-setting tools, accountability measures, and activity trackers, particularly through mobile technology [22,23]. They want these tools to be affordable, convenient, and accessible [22,23].

Research indicates that MS providers also want to support physical activity engagement in their patients with MS [21,24]. Providers recognize the opportunity for patient-provider interactions to discuss and promote physical activity [21,25]. They want clear protocols for prescribing physical activity, including for providing brief advice, discussing the benefits of physical activity, and assessing physical activity behavior [21,25]. They also want tools to help their patients initiate, track, and sustain physical activity and ways to monitor and guide activity [21].

The ExerciseRx app is an innovative cloud-based, Health Insurance Portability and Accountability Act (HIPAA)–compliant software platform that addresses the current gaps in physical activity support in clinical care. The ExerciseRx app was developed at the University of Washington to bridge the gap between consumer activity tracking devices, such as personal smartphones, and the electronic health record (EHR), thus making physical activity support possible in the clinical setting. Currently available apps and devices (eg, Fitbits) are not connected to EHR systems, making it difficult for health care providers to prescribe and monitor their patients’ physical activity. In contrast, the ExerciseRx app translates summative physical activity data collected by the patient’s existing personal smart devices (Android or iOS phone or tablet) into actionable metrics on a provider dashboard within the EHR (Figures 1 and 2). Each patient is provided a personalized recommendation to facilitate an increased step count gradually and safely over time. Providers can also recommend physical activity tailored to patients’ ability levels and preferences. The platform incorporates behavior change strategies, including motivational feedback and nudges. Through its connection to the EHR, it also facilitates a feedback loop with the provider, fostering caring patient-provider connections around activity promotion and behavior change. The ExerciseRx app leverages patients’ personal smartphone capabilities to track, quantify, and tailor personalized physical activity recommendations, which makes it readily scalable, accessible, and affordable across diverse patient populations and clinical settings.

**Figure 1 figure1:**
[figure not shown]
Overview of the ExerciseRx platform.

**Figure 2 figure2:**
[figure not shown]
The ExerciseRx app example screenshots.

This paper describes the rationale, aims, and protocol for the ExerciseRx-MS Trial, a randomized controlled trial designed to answer whether the ExerciseRx platform improves physical activity and other common symptoms and functional outcomes in adults with MS who are insufficiently active. The first aim is to evaluate the efficacy of the ExerciseRx platform relative to usual care in increasing physical activity, measured by average daily step count (primary outcome), activity volume, and the proportion who meet exercise guidelines in adults with MS who are insufficiently active. We hypothesize that participants randomized to the ExerciseRx app group will show a greater increase in physical activity at 12 weeks, as measured by daily average step count (primary outcome) and by total metabolic equivalent minutes of activity per week (secondary outcome) relative to participants randomized to usual care. We also hypothesize that a higher proportion of participants in the ExerciseRx app group will increase their minutes per week of moderate to vigorous intensity aerobic activity at 12 weeks (secondary outcome), relative to usual care participants.

The second aim is to evaluate the efficacy of the ExerciseRx platform relative to usual care on secondary outcomes, specifically symptoms (fatigue intensity, pain intensity, sleep, and depressive symptoms) and patient-reported functional outcomes (physical functioning, fatigue interference, pain interference, falls, and social participation). We hypothesize that participants in the ExerciseRx platform group will show greater improvements in secondary outcomes at 12 weeks relative to usual care participants. Additional secondary analyses will test maintenance of any treatment effects at a 3-month follow-up. We will also explore moderators of immediate (post-12 weeks) and 3-month follow-up outcomes, including demographics, disease course, and baseline participant factors (including fatigue, pain, depression, activity level, BMI, exercise self-efficacy, and disability) to explore potential moderators of treatment effects that can be evaluated a priori in future effectiveness and mechanistic research.

We also plan to evaluate implementation factors relevant to future multicenter effectiveness trials and large-scale implementation of the ExerciseRx platform in MS centers (Aim 3)*.* Both quantitative (usability ratings of ease of use, interface, satisfaction, and usefulness, and the frequency and engagement with the ExerciseRx app) and qualitative data collected from both patients and providers will assess these implementation outcomes.

## Methods

### Design

To address Aims 1 and 2, we are conducting a two-group parallel (1:1) assessor-masked randomized controlled trial designed to compare the ExerciseRx platform to usual care. We will use qualitative research methods to explore implementation factors (Aim 3). Outcomes are being collected at baseline, post a 12-week treatment period (primary end point), and at a 3-month follow-up after the treatment period. We selected a 3-month follow-up because it is feasible in a 3-year study and sufficient time to see a change in activity behavior. We preregistered the trial at ClinicalTrials.gov (NCT06270641) on February 21, 2024, before enrolling the first participant. Figure 3 provides the study design and participant flow.

**Figure 3 figure3:**
[figure not shown]
Overview of the ExerciseRx-MS study design. MS: multiple sclerosis; REDCap: Research Electronic Data Capture.

### Ethical Considerations

All study procedures were approved by the University of Washington Human Subjects Division (STUDY00018628) on August 30, 2023. Electronic informed consent is obtained from all study volunteers at the time of enrollment; they are informed that they can opt out of participation at any time during the study. Some identifiers (eg, name, mailing address, ZIP code, email address, phone numbers, and medical record number) are collected for the trial. To protect identifiable participant data, access is restricted to authorized study personnel who are trained in confidentiality and data security procedures. All electronic data are stored on secure, encrypted servers with access controls. Identifiers are stored separately from research data, and all data transfers use secure, encrypted methods. Participants will be informed of confidentiality protections in the consent process, and data will be securely destroyed when no longer needed. Participants are compensated US $150 for completion of all study assessments (US $50 for each of the three assessment points).

### Setting

Participants (n=106) are being recruited from the University of Washington Medicine Multiple Sclerosis Center, a comprehensive, interdisciplinary center that provides specialty care (including neurology, rehabilitation medicine, and psychology) for >3000 patients with MS per year. All clinic patients are offered opportunities to participate in clinical research through a coordinated research registry recruitment effort that is a standard element of the clinic’s patient flow.

### Recruitment, Enrollment Procedures, and Eligibility Criteria

The primary recruitment sources are referrals from clinic providers (physiatrists, neurologists, nurse practitioners, nurses, and psychologists) and the research registry. The EHRs of patients who are potentially interested in and eligible for the study are prescreened by a research coordinator to confirm MS diagnosis [26,27]. The coordinator then meets with the potential participant by phone to complete a standardized eligibility safety screening to ascertain eligibility. Staff track the recruitment outcomes for everyone who is screened, including reasons for ineligibility or declination. Basic demographic and MS disease characteristics (MS duration, course, and date of diagnosis) are obtained for those considered eligible who decline to enroll; this deidentified information will be used to compare them to study participants to assess the sample’s generalizability. All consent procedures are via REDCap (Research Electronic Data Capture; Vanderbilt University), an open-source, secure, HIPAA-compliant web-based platform for data capture (including e-consent and outcome survey administration) [28].

Inclusion criteria are (1) provider-confirmed diagnosis of MS; (2) 18 years of age or older; (3) Patient Determined Disease Steps (PDDS) score <3, indicating the potential for some gait disability although typically ambulates without an assistive device; [29-31] (4) insufficiently active, defined as <150 minutes of moderate intensity physical activity per week per the US National Physical Activity Guidelines, assessed using the Physical Activity Vital Sign [26,27,32] during screening; and (5) use of an iPhone with software version iOS14+ or an Android phone with version 5+. Exclusion criteria are (1) recent (past 4 weeks) or planned surgery during the study period which may impact step counts; (2) MS relapse within the last 30 days; (3) plans during the study period which may impact a participant’s daily access to Wi-Fi, which could interfere with server uploads of mobile phone data; (4) >3 falls in the past 6 months; and (5) contraindication to exercise.

During the safety screening, through questions adapted from the Physical Activity Readiness Questionnaire [33], participants are asked to report any recent history of chest pain during exercise, loss of consciousness, health conditions worsened by physical activity, and other contraindications to exercise. Participants are also asked if they have a history of osteoporosis. If yes, the research coordinator obtains an electronically signed HIPAA authorization from the potential participant for further screening to be completed by a study investigator.

### Randomization, Allocation Concealment, and Masking Procedures

Block randomization, stratified by self-reported sex assigned at birth, is done using a web-based treatment arm assignment system with a 1:1 assignment after the one-week baseline. To ensure concealed allocation, an unmasked research coordinator retrieves the treatment assignment at the time of randomization and informs the participant of their assignment. The coordinator also notifies the participant’s provider of their assignment to the ExerciseRx app group so that they know to look for the participant on the provider dashboard of the ExerciseRx platform. The statistician is masked to treatment allocation.

Participants directly enter their patient-reported outcomes data into REDCap, the web-based data capture platform, which minimizes concerns of staff biases interfering with data collection. Participants are informed of equipoise and that the study’s purpose is to determine whether the ExerciseRx platform or usual care is more beneficial.

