### Sample Size, Power, and Analysis Plan

Assuming a 15% noncompletion, we plan to enroll 106 participants in the trial to ensure 90 participants complete the study. With 90 participants (45 in each group), we will have 80% power to detect a significant difference in the change in mean daily step count from baseline to 12 weeks between the treatment and control groups for a moderate standardized effect size (Cohen *d*=0.60) using a two-sided significance level of .05.

For Aim 1, we will analyze the efficacy of the ExerciseRx platform using a linear mixed effects model with average daily step count each week as our outcome, fixed effects for week, treatment assignment, and the week-treatment interaction, and a random intercept for each participant. The presence of a significant interaction will indicate that the change in step count over the 12-week study period is impacted by treatment assignment. If differences in demographic or other clinically relevant characteristics between the two groups are found in the descriptive analysis, sensitivity analyses will be conducted, including those characteristics as adjustment variables in the model. Post hoc analyses will include independent and paired sample 2-tailed *t* tests to determine if there are differences between treatment groups at specific time intervals or differences between specific time intervals within a treatment group.

Similar models will be used for Aim 2 and for the secondary physical activity outcomes (activity volume and proportion meeting physical activity guidelines), using each of the secondary outcome measures as the outcome variable in the linear mixed-effects model. As no correction for multiple comparisons will be implemented for these analyses, any significant findings will be considered as hypothesis-generating.

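### The primary mixed model does not use the shared pre-randomisation baseline, which gives away some precision; a common-baseline constraint, sex and a fixed covariate list should be prespecified

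*Protocol article*

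**What the plan says.** Under Randomization, Allocation Concealment, and Masking Procedures, the protocol article describes "Block randomization, stratified by self-reported sex assigned at birth", with 1:1 assignment once the one-week baseline is complete. Under Primary Outcome: Step Count, steps are recorded passively in both arms during that week and through the 12 intervention weeks.

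Under Sample Size, Power, and Analysis Plan, the primary model takes weekly mean daily steps as its outcome, with "fixed effects for week, treatment assignment, and the week-treatment interaction, and a random intercept for each participant". The interaction is the test of efficacy. The power statement concerns "a significant difference in the change in mean daily step count from baseline to 12 weeks between the treatment and control groups": "With 90 participants (45 in each group), we will have 80% power" at a standardised effect of 0.60, "using a two-sided significance level of .05".

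Other characteristics enter by this rule: "If differences in demographic or other clinically relevant characteristics between the two groups are found in the descriptive analysis, sensitivity analyses will be conducted". The same type of model is carried over to the secondary outcomes.

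The article does not say whether the baseline week is one of the outcome weeks, or whether week is categorical or linear.

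**The concern.** Baseline steps are measured before assignment, so the two arms share one expected baseline mean. A free treatment main effect makes the model estimate a baseline difference whose expectation is zero. The estimated change then carries the noise of that estimate. With the baseline week as an outcome row and week as a category, the week-12 interaction term is a comparison of change scores. That comparison is less efficient than one that uses the common baseline.

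There are two smaller points. Sex governs the randomisation but does not appear in the model. And the covariates for the sensitivity analyses depend on which differences show up in the descriptive tables, with no list and no threshold given. After randomisation, observed imbalance is chance and does not show which variables are prognostic.

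At stake are the width of the confidence interval for the primary effect and how clearly the supporting analyses are fixed in advance. The validity of the primary test is not at stake.

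**Working it through.** **Inputs from the article.** 45 completers per arm; d = 0.60, read as being in SD units of the change score, because change is what is powered; two-sided alpha 0.05; 15% noncompletion; 106 enrolled.

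**Assumed.** The baseline-to-week-12 correlation r is not given; 0.6 to 0.9 is shown. Variance is taken as equal across weeks, as the random-intercept model implies, and weeks as complete.

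**Step 1: the stated design.** Noncentrality = d × √(n/2) = 0.60 × √22.5 = 2.846 on 88 degrees of freedom. Power is 80.4% (noncentral t), or 81.2% by the normal approximation. The smallest n per arm for 80% power is 45 (noncentral t). Enrolment is 90 / 0.85 = 105.9, rounded up to 106. The article's figures reproduce.

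**Step 2: week categorical, baseline week as an outcome row.** With σ² the variance of weekly steps, the per-person variance is 2σ²(1 − r) for the change score and σ²(1 − r²) with baseline adjusted or constrained. The ratio is (1 − r²) / [2(1 − r)] = (1 + r)/2. The generalised least squares variance of the stated random-intercept model over weeks 0 to 12, with and without the treatment effect at week 0, gives the same ratios. Power is recomputed at an effective d of 0.60 / √((1 + r)/2).

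| r (assumed) | Variance ratio | Effective d | Power, 45 per arm | n per arm for 80% |
|---|---|---|---|---|
| as stated | 1.00 | 0.600 | 80.4% | 45 |
| 0.6 | 0.80 | 0.671 | 88.2% | 36 |
| 0.7 | 0.85 | 0.651 | 86.3% | 39 |
| 0.8 | 0.90 | 0.632 | 84.3% | 41 |
| 0.9 | 0.95 | 0.616 | 82.3% | 43 |

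**Step 3: week linear, weeks 0 to 12.** With t = 0, …, 12: Σt = 78, Σt² = 650, and the centred sum of squares is 650 − 78²/13 = 182. With a free treatment main effect, the information on the slope difference is proportional to 182. With a common baseline it is proportional to 650 − 6084 × r/(1 + 12r). The variance ratio is 182 divided by that quantity:

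- r = 0.6: 182 / 204.8 = 0.889, a saving of 11%
- r = 0.7: 182 / 196.9 = 0.924, a saving of 8%
- r = 0.8: 182 / 190.8 = 0.954, a saving of 5%
- r = 0.9: 182 / 186.0 = 0.979, a saving of 2%

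**Step 4: sex.** The interaction is a within-person contrast, so a term that is constant over weeks cancels. Adding a sex main effect to the stated model gives a variance ratio of 1.000. Once baseline is constrained, sex saves about 0.2% to 1.2% of variance (assumed: 75% female, a gap in step level of 0.3 to 0.5 SD, r of 0.6 to 0.8). A sex-by-week term helps only if change differs by sex. At 75% female and an assumed gap of 0.5 SD of change, it explains 0.1875 × 0.25 / (1 + 0.1875 × 0.25) = 4.5% of the variance.

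**The case against.** The strongest reply is that nothing here is invalid. Randomisation makes the unadjusted interaction unbiased, and the planned power does not rely on adjustment. Both statements are correct, and they make this a point about efficiency and prespecification.

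It can also be said that the size is unknown. That stands too. The article gives no correlation, and daily steps are likely to be strongly person-specific. At r = 0.9 the gain is about 2 percentage points of power, and a linear week shrinks the saving further. If the baseline week is not an outcome row, the percentages above do not apply directly, and the baseline would have to enter as a covariate or be added as a row.

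The article condenses a fuller plan, which may settle these matters. But it names the primary model's terms and its test explicitly, so this is a stated choice and not simply an omitted detail.

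Two stronger readings are tempting. A reader might infer that leaving out sex wastes precision or distorts the standard error of the primary test. Step 4 shows no material effect on the interaction; the argument for sex is that the analysis should follow the randomisation. A reader might also infer that chance imbalance will decide the primary estimate. The article confines that rule to sensitivity analyses, so the primary model stays the same whatever the baseline tables show.

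**Conclusion.** The point holds as an improvement that should be made. The stated model leaves unused the knowledge that both arms share one baseline mean, and so gives up precision that needs no further participants. For a week-12 contrast with categorical week, the variance saving is 20% to 5% and power rises from 80% to between 88% and 82% as r goes from 0.6 to 0.9. For a linear week the variance saving is 11% to 2%. Within this range the change never costs precision.

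These sizes rest on an assumed correlation, equal variances, complete weeks, the baseline week being an outcome row, and d being expressed in change-score SD units. That there is a gain is well supported; its size is only moderately certain. Including sex is a matter of consistency with the design. The imbalance-triggered covariates are a minor weakness of the sensitivity analyses.

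**What to change.** - **Primary model.** Enter the baseline week as an outcome row with no treatment effect at week 0, so that the arms share a baseline mean. Alternatively, model weeks 1 to 12 with baseline steps by week as a covariate. State which is used and whether week is categorical or linear.
- **Sex.** Add it as a fixed effect because it is the stratification factor, and claim no material precision gain for the interaction.
- **Continuous secondary outcomes.** Treat each outcome's own baseline in the same way. This adds little for the proportion meeting activity guidelines, because eligibility requires being below the activity threshold at screening.
- **Sensitivity analysis.** Replace the imbalance trigger with a short list chosen for prognostic value and fixed before unmasking. Age and PDDS are collected on everyone and are candidates, although eligibility narrows the range of PDDS.

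The cost is wording in the analysis plan. No new data, participants or procedures are needed. The article describes the statistician as masked and puts the start of analysis in January 2026, so the change should be dated and recorded before allocation is revealed.
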